### 6.8.2 Screening and eligibility

Between day -21 and day of surgery, after obtaining informed consent (as described in Section 6.1), subjects who fulfill all of the inclusion criteria and none of the exclusion criteria will be accepted into the study. Documentation of the fulfillment of criteria will be included in the study files.

### 6.8.3 Study completion

Subjects who attend the 6-month study visit and have completed all study-related evaluations described in Section 6.5.2 will be considered as having completed the study.

Subjects who elect to discontinue pre-maturely or are withdrawn from the study by the investigator, will be converted to standard of care treatment alone (no further study imaging/ultrasound). If it is not possible to complete the end-of-study visit, every attempt will be made to determine safety endpoints (adverse events, breast cancer recovery status) occurring since the previous visit. A phone visit may be utilized for this information if the subject is unable or unwilling to attend the next or last study visit.

Subjects will be followed as standard of care after the study regimen has been completed or discontinued.

## 7 Statistical analysis plan

### 7.1.1 Sample size

This single-center study will enroll up to 15 de novo breast conserving therapy subjects. This is a prospective, pilot, observational study. Subjects withdrawn from the study cannot re-enter. Up to 3 patients, if withdrawn prior to week 6, will be replaced. Twelve subjects will be considered

evaluable if they complete up to visit 5 and will be considered completers if they complete all study visits and procedures.

### 7.1.2 Preliminary Data Analysis Plan

Evaluable subjects will have completed a minimum of 5 visits (week 6). Descriptive statistics will be used to summarize the demographic and clinical characteristics of subjects. Changes at the end of study from baseline will be evaluated using chi-square for categorical variables and Kruskal-Wallis for continuous variables.

Receiver operator characteristic curves will be used to explore the sensitivity of the multiscale model to the outcome.

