## **3 Design rationale**

The proposed study is a single-center, prospective, pilot observation study to tabulate and measure the changes that occur during treatment and healing for BCT in women with non-metastatic breast cancer for comparison to the multiscale model of breast lumpectomy and healing in order to identify targets for improving BCT.

There is currently no information on which to base a prediction of breast contour following BCT, but the problem of cosmesis following BCT is substantial for many patients. The data collected in this observational study will provide a basis for testing the predictability of the multiscale model of breast lumpectomy and healing.

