## 4 Experimental plan

### 4.1 Study design

This is a single-center, prospective, pilot observation study. Eligible subjects who enroll in this study will begin at the time of informed consent, which will occur during the pre-operative, surgical evaluation time.

The study plan demonstrates when subjects will have their surgery and when subjects will have study visits (Figure 1). The planned procedures are detailed in section 5 and the schedule of events table in section 6.

[figure not shown]

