#### 4.1.2 Number of subjects

Up to 15 de novo breast cancer subjects will be enrolled in order to allow for early drop-outs resulting in 12 evaluable cases.

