## **6.4 3-Dimensional Surface Imaging of the Breast**

A 3-dimensional 180° camera will be used to capture surface imaging prior to surgery and at three time-points after surgery (visits 2, 4 and 6). The surface imaging will provide measures of breast deformity.

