## **6.6 Pain scale score**

Pain will be assessed prior to surgery and at each follow-up visit prior to the ultrasound procedure and following the ultrasound procedure.

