## **6.8 Judging**

Breast cosmesis will also be assessed using the 4-point Harvard/NSABP/RTOG cosmesis criteria scale (Appendix) and judged by two independent surgeons not involved in the care of the patient or the study. Judging will occur at baseline (after surgery) and at week 10 and week 26.

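### Section 7.1.2 tests within-patient change from baseline with independent-group tests (chi-square, Kruskal-Wallis), so the p-values are miscalibrated unless a woman's two measurements are uncorrelated

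*Protocol*

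**What the plan says.** Protocol section 7.1.2 (Preliminary Data Analysis Plan) names the tests: "Changes at the end of study from baseline will be evaluated using chi-square for categorical variables and Kruskal-Wallis for continuous variables". No paired test is named anywhere in the protocol.

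The design has one cohort. Section 4.1: "This is a single-center, prospective, pilot observation study". Section 3 describes it as a "single-center, prospective, pilot observation study to tabulate and measure the changes that occur during treatment and healing". Section 4.1.2 gives the size: "Up to 15 de novo breast cancer subjects will be enrolled in order to allow for early drop-outs resulting in 12 evaluable cases". No subject groups are defined.

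The same women are measured repeatedly:
- Surface imaging is done once before surgery and at visits 2, 4 and 6 (section 6.4).
- Pain, section 6.6: "Pain will be assessed prior to surgery and at each follow-up visit".
- Cosmesis on the four-point scale, section 6.8: "Judging will occur at baseline (after surgery) and at week 10 and week 26".
- Thermal imaging and ultrasound are done at visits 2 to 6 (schedule in section 6.8.1).

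The protocol states no significance level, effect size, standard deviation or within-woman correlation.

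**The concern.** With one cohort, a change from baseline to the end of the study compares two values from each woman. Kruskal-Wallis applied to two time points is a rank-sum test for two independent samples. Chi-square on a time-by-category table treats 12 earlier and 12 later values as 24 different people. Neither uses the pairing.

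If a woman's two values are positively correlated, as one would usually expect, the difference varies less than these tests assume. The p-values are then too large and a real change can be missed. If the correlation were negative, they would be too small. The results at stake are the descriptions of change in surface contour, lumpectomy bed, temperature and pain, which are secondary objectives in section 2.2.2. The sentence is a rule the protocol itself states, not a detail left to a separate analysis plan.

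**Working it through.** **The plan's own figure.** Section 7.1.1 allows this: "Up to 3 patients, if withdrawn prior to week 6, will be replaced". 12 evaluable + 3 replacements = 15 enrolled, which agrees with section 4.1.2. This is a headcount; there is no power calculation to reproduce.

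**Inputs.** From the protocol: one cohort and 12 evaluable women. Assumed, because not stated: two-sided 5%; 12 complete pairs (a woman is evaluable at visit 5, so fewer or more than 12 could contribute at visit 6); normally distributed values; shifts of 0.5, 0.8 and 1.0 SD; a range of correlations.

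**Direction.** The variance of the difference between the two time-point means is 2σ²(1 − ρ)/n. An independent-group test takes it as 2σ²/n. At ρ = 0.5 the true variance is half of what the test assumes, and at ρ = 0.7 it is 30%.

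**Kruskal-Wallis, two time points.** H = 12/[N(N+1)] × ΣR²/n − 3(N+1), with N = 24 and n = 12, referred to chi-square on 1 df (critical value 3.84). With rank sums of 116 and 184, H = 0.02 × (13,456 + 33,856)/12 − 75 = 3.85, which just rejects.

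**Wilcoxon signed-rank.** Exact null distribution for 12 differences.

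20,000 simulated data sets per setting gave:

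| Correlation | KW true size | Signed-rank true size | Power at 0.8 SD, KW | Power at 0.8 SD, signed-rank |
|---|---|---|---|---|
| −0.3 | 8.4% | 4.2% | 45.6% | 31.1% |
| 0 | 5.2% | 4.2% | 45.5% | 38.9% |
| 0.3 | 2.6% | 4.4% | 45.4% | 52.9% |
| 0.5 | 1.0% | 4.2% | 44.7% | 67.0% |
| 0.7 | 0.2% | 4.2% | 45.0% | 87.5% |

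A repeat simulation gave 47% v 40% at correlation 0 and 46% v 54% at 0.3, so these powers should be read to within one or two points.

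**Relative loss of power, (signed-rank − KW)/signed-rank:**
- 0.8 SD: (52.9 − 45.4)/52.9 = 14% at correlation 0.3; (67.0 − 44.7)/67.0 = 33% at 0.5; (87.5 − 45.0)/87.5 = 49% at 0.7.
- 0.5 SD: (31.7 − 15.0)/31.7 = 53% at 0.5; (48.7 − 11.6)/48.7 = 76% at 0.7.
- 1.0 SD: (85.2 − 68.0)/85.2 = 20% at 0.5; (97.2 − 72.1)/97.2 = 26% at 0.7.

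**Binary variables, 12 pairs from correlated latent normals.** With a true proportion of 50% at both times, the size of chi-square is 6.1%, 2.3% and 0.5% at latent correlation 0, 0.5 and 0.8; exact McNemar gives 1.2%, 0.5% and 0.1%. For a change from 20% to 60%, chi-square has about 57% power at each of these correlations, and exact McNemar 31% to 34%.

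**Sparse tables.** With 12 values at each time, each expected count is half its category total, so a category needs a total of 10 to reach 5. Three such categories would need 30 values and there are 24. If three or more cosmesis levels occur, some expected counts must fall below 5.

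**The case against.** Four points can be made for the other side.

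1. **Another reading makes the tests admissible.** Change scores could be compared between subgroups of women. This does not stand: the sentence names no subgroups and the protocol defines none.

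2. **The loss of power is not established.** A reader might infer that most of the power is always lost. The documents do not support that. They give no correlation or effect size, and surgery and radiotherapy fall between the first and last measurements, so the correlation could be modest. At correlation 0 nothing is lost, at 0.3 the loss is small, and a loss above three quarters needs a small shift (0.5 SD) with a correlation of 0.7 or more. This objection stands, and the size of the problem has to be given as conditional.

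3. **The power argument does not carry over to categorical variables.** A reader might extend it to chi-square. At 12 pairs, exact McNemar is more conservative and less powerful than chi-square. This stands. The reason to change is that the analysis should respect the pairing.

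4. **Little depends on these p-values.** A reader might infer that the study's main conclusion is at risk. It is not: the primary quantitative criterion is a mean agreement of at least 60% with the model (sections 4.1.1 and 7.1.3) and uses neither test. The section is headed as preliminary, the secondary aims are largely descriptive, cosmesis is to be summarised, and no significance threshold is set. This stands and limits the severity. It does not make the named tests right.

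**Conclusion.** The point holds in a limited form. Section 7.1.2 names independent-group tests for within-woman change in a single cohort, and the p-values are miscalibrated unless the two measurements are uncorrelated. Under the assumptions above, the true size of Kruskal-Wallis at a nominal 5% falls from about 5% at correlation 0 to 1.0% at 0.5 and 0.2% at 0.7. For a 0.8 SD change the signed-rank test has no advantage at correlation 0, and gains about 22 points at 0.5 (67.0 − 44.7) and 42 at 0.7 (87.5 − 45.0).

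That the size is wrong whenever the correlation is not zero follows from the design. How far it is wrong, and how much power is lost, rests on a correlation the protocol does not give. The sentence should be corrected, but the flaw is not critical to this pilot.

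**What to change.** Replace the sentence in section 7.1.2 with paired methods:
- Continuous variables and the ordinal cosmesis score: Wilcoxon signed-rank test on the within-woman change, in an exact form that allows for ties and zero differences. If all visits are used, a Friedman test or a mixed model with a subject effect.
- Binary variables: a McNemar-type test, chosen because it is a valid paired analysis and not because it adds power.
- In all cases, report the median paired change or the paired difference in proportions with a 95% confidence interval. With 12 women the estimate and its interval say more than the p-value.

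Also state which measurement is the baseline for each variable: cosmesis, ultrasound and thermal imaging are first recorded after surgery, surface imaging and pain before it.

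The cost is a few lines of analysis wording. No additional subjects, visits or measurements are needed.

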#### **2.2.2 Secondary objective**

Secondary objectives are to

- provide information regarding the use of 3-dimensional surface imaging to detect changes over time in the skin surface and dimension related to lumpectomy healing and breast contour
- provide information on the use of ultrasound of the lumpectomy bed and changes that occur during the course of breast cancer treatment and healing
- provide information on thermal imaging and inflammation symptoms
- to describe the course of pain experienced by women undergoing BCT and the correlation of pain to the healing process.

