## **6.5 Breast Ultrasound**

Breast ultrasound will be performed in the outpatient surgery clinic at visits 2, 3, 4, 5, and 6 using an office-application ultrasound system with a soft-tissue transducer, such as the SonoSite EDGE™ machine with HFL50x or HFL38x transducer.

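### The one named test of change across visits compares end of study with baseline, which does not match secondary objectives about the course of pain and healing

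*Protocol*

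**What the plan says.** Protocol Section 7.1.2: "Changes at the end of study from baseline will be evaluated", by chi-square where the variable is categorical and by Kruskal-Wallis where it is continuous. The descriptive statistics in the same section are for demographic and clinical characteristics; no by-visit summary is named.

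The secondary objectives in Section 2.2.2 are worded around time:

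- Pain: "to describe the course of pain experienced by women undergoing BCT and the correlation of pain to the healing process".
- Surface imaging: "provide information regarding the use of 3-dimensional surface imaging to detect changes over time in the skin surface and dimension related to lumpectomy healing".
- Ultrasound: "provide information on the use of ultrasound of the lumpectomy bed and changes that occur during the course of breast cancer treatment and healing".

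The synopsis adds thermal imaging to capture what happens during healing, and Section 4.1.1.2 lists pain across the six months as a secondary variable.

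The schedule in Section 6.8.1 is built for this. It places visits 2 to 6 at weeks 1, 3, 6, 12 and 24. Section 6.5 states: "Breast ultrasound will be performed in the outpatient surgery clinic at visits 2, 3, 4, 5, and 6". Thermal images follow the same visits. Surface images are taken before surgery and at visits 2, 4 and 6 (Section 6.4). Pain is scored once before surgery and twice at each later visit, before and after the ultrasound (Section 6.6).

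Section 7.1.3 lists further outcomes: pain of 8 or more on more than one post-operative measurement, a rise of 3 or more units from before to after ultrasound at each visit, change in the thermal image, agreement with the model at weeks 10 and 26, and a cosmesis summary at weeks 10 and 26.

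**The concern.** A contrast between two time points estimates a net difference, not a course. Pain after surgery and radiotherapy can rise and then settle. If it has settled by the last visit, the end-of-study change is near zero however large the rise was. The study could then report no change on a measure whose path it set out to describe, although the repeated scans and scores had been collected.

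The issue is which time points are compared, not which test compares them. A paired test on the same two visits would have the same limit.

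**Working it through.** The plan states no figure for this point (no power, effect size or error rate), so there is none to reproduce. The check is a count, a look at what the contrast estimates, and a reading of Section 7.1.3.

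**1. Data outside a first-versus-last contrast.** Inputs: the schedule in Section 6.8.1, Sections 6.4 to 6.6, and 12 evaluable women (Section 4.1.2). The last column assumes that all 12 complete every visit.

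| Measure | Weeks | Per completer | Used | Outside | Outside, 12 women |
|---|---|---|---|---|---|
| Pain score | pre-surgery, 1, 3, 6, 12, 24 | 1 + 2×5 = 11 | 1 + 2 = 3 | 11 − 3 = 8 | 96 of 132 |
| Surface image | pre-surgery, 1, 6, 24 | 4 | 2 | 2 | 24 of 48 |
| Thermal image | 1, 3, 6, 12, 24 | 5 | 2 | 3 | 36 of 60 |
| Ultrasound | 1, 3, 6, 12, 24 | 5 | 2 | 3 | 36 of 60 |

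For pain, both visit 6 scores are counted as used.

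**2. What the contrast estimates for pain.** Write m(t) for the mean at week t and m(pre) for the pre-surgery mean. The contrast is m(24) − m(pre). The documents give no expected pain levels, so the following means (pre-surgery, then weeks 1, 3, 6, 12, 24) are assumptions that only show the arithmetic:

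- 1, 5, 4, 3, 2, 1: changes from pre-surgery are +4, +3, +2, +1, 0; the contrast is 1 − 1 = 0.
- 1, 7, 6, 4, 2, 1: changes are +6, +5, +3, +1, 0; the contrast is again 0.
- Either path ending at 2 instead of 1: the contrast is +1, against a peak change of +4 or +6.

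So the contrast shows what remains at week 24 and nothing of the size or timing of the rise.

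**3. What it estimates for thermal imaging and ultrasound.** There is no pre-surgery value, so the contrast can only be m(24) − m(1). With assumed departures at weeks 1, 3, 6, 12 and 24:

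- 2, 1.5, 1, 0.5, 0: contrast 0 − 2 = −2. Inflammation already present at week 1 that resolves appears as a fall.
- 0, 0.7, 1.5, 0.7, 0: contrast 0. A rise after week 1 that returns to the week 1 level is hidden.

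**4. Whether Section 7.1.3 supplies the course.**

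- Pain of 8 or more on more than one measurement spans all post-operative scores, but it is a threshold. A woman scoring along either path in step 2 is never counted, and the outcome does not say when pain occurred.
- The rise of 3 or more units is a difference within a visit. A woman scoring 5 before and 5 after ultrasound at week 1 contributes the same zero as one scoring 1 and 1 at week 24.
- Thermal change is listed without time points or method.
- Model agreement compares measured with predicted values at weeks 10 and 26, where the schedule places only cosmesis judging. It is not a change across visits.
- The cosmesis summary does not concern pain, temperature or lumpectomy dimensions.

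**5. Women without visit 6.** Section 7.1.1 defines evaluable by visit 5 and Section 7.1.2 by five visits (week 6). On either definition an evaluable woman need not have a visit 6, and she then contributes nothing to the end-of-study contrast.

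**The case against.** The best defence has four parts.

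- **Section 7.1.2 is not the whole analysis.** A reader might infer that it is the sole analysis of change, or that healing, temperature and pain between the end visits go unexamined. The document does not support that. Section 7.1.3 uses pain at every post-operative visit and lists thermal change and model agreement on healing as outcomes. This stands, and it limits the point to the absence of any estimate across visits.
- **The objectives are descriptive.** Section 3 says that changes during treatment and healing will be recorded and measured, and description needs no hypothesis test. So it does not follow that the study cannot describe the course. The remedy should therefore be estimates rather than more tests. But the analysis section does not carry this intention into a by-visit summary, and it fixes a different contrast.
- **No change is not the result for every measure.** A reader might extend the pain argument to temperature and ultrasound. Without a pre-surgery value, a resolving week 1 inflammation shows as a fall. For contour, the lasting deformity matters and end versus baseline is a relevant contrast. Both stand.
- **A longitudinal model belongs in a statistical analysis plan, and this section is headed preliminary.** The choice of model can indeed be left there. The point does not rest on a missing model, but on a time contrast that the protocol fixes and that does not fit its own objectives.

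Simulated power for a pain path that starts and ends at the same level would add nothing. The end-versus-baseline difference is then zero by assumption, and such a test rejects only at its false-positive rate.

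**Conclusion.** The concern holds in a limited form. The one named test of change across visits does not match the secondary objectives, and no other stated outcome estimates the course of pain, temperature, lumpectomy dimensions or contour. Between half (surface images) and about 73% (8 of 11 pain scores) of the scheduled measurements lie outside that contrast.

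The consequence is firmest for pain: a moderate rise that resolves by week 24 has an expected change of zero. For thermal imaging and ultrasound, only the net difference from week 1 to week 24 is seen. The counts come from the schedule. The consequence for pain assumes that the rise has resolved by week 24, which the documents neither state nor exclude; if resolution is partial, the contrast shows only the remainder.

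This affects secondary objectives of a pilot, not its primary agreement criterion. It is worth correcting because the data are already being collected.

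**What to change.** In Section 7.1.2, replace the sentence on end-of-study change, for its continuous measures, with wording to this effect: each repeated continuous measure (pre-ultrasound pain, surface temperature, lumpectomy dimensions, surface contour) is summarised at every visit at which it is scheduled, with mean and 95% CI, using all available visits. A linear mixed model with visit as a factor and a random woman effect is one suitable method. End of study versus baseline is kept as one contrast. Baseline is the pre-surgery visit for pain and surface contour, and week 1 for thermal imaging and ultrasound.

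This also uses the visits of women who lack visit 6.

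Cost: a change of wording and slightly more analysis; no new visits, measurements or patients. By-visit estimates will be imprecise. With 12 women, the half-width of a simple 95% CI for a mean is 2.201 × SD/√12 ≈ 0.64 SD (t quantile on 11 degrees of freedom). For an assumed pain SD of 1 to 2 points, that is about ±0.6 to ±1.3 points. The intervals should be reported as descriptive.

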### 7.1.3 Evaluation criteria:

- The primary outcome measure will be
- Qualitative:
  - confirmation that relative size of the lumpectomy to the breast, tissue composition ratio of fat versus glandular, and location of the tumor will provide a qualitative grading of the potential cosmetic outcome.
  - correlation of the wound edge shape to mechanical stress
  - correlation of volume loss due to healing to cosmesis outcome.
- Quantitative: a combined score of the correlation between three measured processes (lumpectomy dimensions, lumpectomy healing process, surface contour changes) and the predicted outcomes from the multiscale model measured/assessed at weeks 10 and 26 postsurgery with a mean accuracy rate of  $\geq 60\%$ .
- Secondary outcome measures will include postsurgery:
  - the proportion of subjects experiencing pain  $\geq 8$  on more than one measurement post operatively and the relationship of pain to the accuracy of the multiscale model
  - the proportion of subjects experiencing increased pain ( $\geq 3$  unit increase) pre to post ultrasound at each visit to determine the possible invasiveness of these multiple post-surgery ultrasounds
  - detection of changes in the thermal image of the breast tissue related to inflammation and healing
  - the summary of the independent judgment (Harvard/NSABP/RTOG scale score) of cosmesis taken at weeks 10 and 26

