##### 4.1.1.1 Primary variables

The primary variables will be surface contour captured by the 3-dimensional 180° camera, lumpectomy dimensions captured by ultrasound, predicted surface contour and predicted lumpectomy dimensions from the multiscale model.

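### The quantitative primary score is set at weeks 10 and 26, but no 3-D image or ultrasound is scheduled in reach of either week; the week 10 surface contour is the material gap

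*Protocol*

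**What the plan says.** Section 7.1.3 defines the quantitative primary outcome as a combined score over "three measured processes (lumpectomy dimensions, lumpectomy healing process, surface contour changes"), each set against the multiscale model, with a mean accuracy of at least 60%. Its timing is "measured/assessed at weeks 10 and 26 postsurgery".

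Section 4.1.1.1 names the instruments: "surface contour captured by the 3-dimensional 180° camera, lumpectomy dimensions captured by ultrasound". Section 6.7 assigns assessment of healing to the thermal camera.

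The imaging times are given in prose and again in the section 6.8.1 table:

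- 3-D surface imaging (6.4): "prior to surgery and at three time-points after surgery (visits 2, 4 and 6").
- Ultrasound (6.5): "performed in the outpatient surgery clinic at visits 2, 3, 4, 5, and 6".
- Cosmesis (6.8): "Judging will occur at baseline (after surgery) and at week 10 and week 26".

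In the table, the week 10 and week 26 columns have no visit number and no window. Their only mark is cosmesis judging. The footnote to that row says that the judging includes a comparison with the model. Section 4.1.1.2 lists the reviewers' judgment of cosmesis against the model as a secondary variable.

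**The concern.** The primary score needs a measured contour and a measured lumpectomy cavity to set against the model's predictions. At the two weeks named for the score, the protocol collects neither. Section 7.1.3 therefore conflicts with sections 6.4, 6.5 and 6.8.1, and the protocol does not say which visit's data stand in.

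The study's purpose is to test predictive validity through treatment and healing, when the breast is expected to change. If a week 10 prediction is set against a contour taken at week 6, the disagreement contains both the model's error and whatever change occurred in the intervening weeks. The two cannot be separated afterwards, and the sum is what is judged against 60%. An image not taken at week 10 cannot be recovered later.

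**Working it through.** The protocol gives no figure to reproduce here. The check is whether either stated week falls inside any permitted imaging interval.

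**Inputs** (section 6.8.1 table; visits confirmed by 6.4 and 6.5)

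| Visit | Week | Window | 3-D image | Ultrasound |
|---|---|---|---|---|
| 2 | 1 | 0 days | yes | yes |
| 3 | 3 | ±7 days | no | yes |
| 4 | 6 | ±7 days | yes | yes |
| 5 | 12 | ±7 days | no | yes |
| 6 | 24 | ±7 days | yes | yes |

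**Step 1: permitted intervals.** Interval = scheduled week ± window in days / 7.

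- Visit 2: week 1 only
- Visit 3: 3 ± 1 = weeks 2 to 4
- Visit 4: 6 ± 1 = weeks 5 to 7
- Visit 5: 12 ± 1 = weeks 11 to 13
- Visit 6: 24 ± 1 = weeks 23 to 25

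Week 10 lies between the visit 4 and visit 5 intervals. Week 26 lies after the visit 6 interval. Neither is inside any of them.

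**Step 2: distance to the nearest measurement.**

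| Target | Measure | Nearest visit | Nominal gap | Range with window |
|---|---|---|---|---|
| Week 10 | 3-D contour | 4 (week 6) | 10 − 6 = 4 weeks early | 10 − 7 = 3 to 10 − 5 = 5 weeks early |
| Week 10 | Ultrasound | 5 (week 12) | 12 − 10 = 2 weeks late | 11 − 10 = 1 to 13 − 10 = 3 weeks late |
| Week 26 | 3-D contour and ultrasound | 6 (week 24) | 26 − 24 = 2 weeks early | 26 − 25 = 1 to 26 − 23 = 3 weeks early |

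**Step 3: the contour gap around week 10.** The next 3-D image after visit 4 is visit 6. The latest permitted visit 4 is week 7 and the earliest permitted visit 6 is week 23, so no contour image is planned between weeks 7 and 23. For week 10, the contour would have to be carried forward from visit 4 or interpolated between visits 4 and 6.

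**Step 4: the healing component.** The thermal row of the table is marked at weeks 1, 3, 6, 12 and 24, the same weeks as ultrasound. It does not reach week 10 or week 26 either.

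**Step 5: is this an artefact of a broken table?** No. The prose in 6.4 and 6.5 names the same visits as the table. The synopsis plans six visits apart from surgery, and all six are assigned to other weeks, so there is no unlisted visit at week 10 or 26.

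**The case against.** The strongest reply is that section 7.1.3 does not say that images are taken at weeks 10 and 26. Its wording covers assessment as well as measurement, and the footnote to the judging row mentions comparison with the model. Those weeks could be when stored images are compared with the model. Three post-surgery 3-D images (weeks 1, 6 and 24) would match three judging times (after surgery, week 10, week 26). On that reading the score can be computed, and nothing in the protocol stops the team from running the model to the date of each image.

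Much of this stands. A reader might infer that the primary outcome cannot be computed at all, or that none of its inputs exist. The documents do not support that, because the stored-image reading is coherent. It is also unstated, however: no section says which image serves which week, and the comparison in the footnote may be only the secondary cosmesis variable of 4.1.1.2.

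A reader might also infer that radiotherapy is under way at week 6 and over by week 10, because the table marks it at week 6 and not at week 10. The week 10 column has no visit and a single entry, so its blank shows nothing about radiotherapy. Section 5.1 gives fraction counts but no start or end date.

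The gaps are also unequal. Week 26, and week 10 ultrasound, are 1 to 3 weeks from a scheduled visit; naming that visit would largely settle them. Week 10 contour has no comparable remedy in the present schedule.

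Finally, this is a small observational pilot aiming for 12 evaluable subjects. That limits the consequences, but the 60% criterion still needs defined inputs.

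**Conclusion.** The point holds as an internal conflict over the timing of the primary score. Neither stated week falls inside any permitted 3-D imaging or ultrasound interval. The serious part is week 10 surface contour: 4 weeks from the nearest image nominally, 3 to 5 with the window. The remaining gaps are 2 weeks nominally, 1 to 3 with the window.

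This rests on the visit weeks and windows in section 6.8.1 and on the instruments named in 4.1.1.1. The mixing of date mismatch with model error is conditional: it arises if predictions are made for weeks 10 and 26 and compared with images from other dates. The protocol neither requires nor excludes that. Its effect on the 60% result cannot be put in numbers, because the protocol gives no rate of change for contour or cavity size.

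**What to change.** In section 7.1.3, replace weeks 10 and 26 for the quantitative score with visit 4 (week 6) and visit 6 (week 24). These are the two later follow-up visits with both 3-D imaging and ultrasound; visit 2 at week 1 also has both. State that the model is run to each subject's actual imaging date, so that variation within the visit window does not enter the score.

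If week 10 or week 26 matters scientifically, move an existing imaging visit to that week instead. For week 10 the moved visit must carry the 3-D image: moving visit 5 alone would bring ultrasound but no contour.

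Cosmesis judging may stay at weeks 10 and 26 as a secondary outcome, with a sentence in 6.8 saying which imaging visit each judgment is compared with. It should not simply be transferred to stored images, because the scale in Appendix 16.3 includes how the breast feels.

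The cost is a protocol amendment with no added visit or image. Under the first option the primary times become weeks 6 and 24, so the intermediate comparison falls earlier in healing. Under the second, the measurement at the vacated week is lost. Either is best settled before enrolment.
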